### Grouping schemes

2.4

According to the cluster randomized study design, each community serves as a cluster. The statistician uses a computer-generated random sequence to independently and with equal probability assign each cluster to one of the three groups (simple cluster randomization): (1) blank control group (no screening group), (2) routine screening group, and (3) tiered screening group. To set up blank controls can analyze the clinical significance and health economic value of routine screening mode for the early diagnosis and treatment of glaucoma. On this basis, it is sufficient to compare the difference in efficiency and cost-effectiveness between the routine screening mode and the tiered screening mode. Baseline data and follow-up outcomes are collected uniformly for all participants.

The control group (no screening group) does not undergo any glaucoma screening, and the study subjects can detect and confirm glaucoma through active medical visit or opportunistic screening. The routine screening group is screened with IOP measurement combined with fundus photography to detect glaucoma. The three-tiered screening model designed in this study is adopted in the tiered screening group. It is expected that high-risk populations of glaucoma are identified in the tier 1 screening, who will enter the tier 2 and/or 3 screenings to diagnose or exclude glaucoma (Figure 1).

**Figure 1 fig1:**
[figure not shown]
Methodology flowchart of the study. AI, artificial intelligence.

The screened high-risk populations, suspected patients, and diagnosed glaucoma patients from all the three groups will receive standard glaucoma treatment and AI-assisted intelligent follow-up of chronic disease management, including health education, subsequent visit reminders and medication guidance, so as to expand the coverage and reduce the labor cost of follow-up.

A no-screening control arm is included in this study, in which participants will not receive any ophthalmic examinations actively provided by the study protocol. As the study population consists of community-dwelling individuals rather than confirmed patients, the absence of active screening does not pose additional disease-related risks to the participants. Subjects in the control arm remain free to seek medical attention if symptoms arise or to undergo opportunistic screening through routine healthcare encounters. Therefore, enrollment does not restrict their access to external medical services or affect their standard of care.

To strengthen the ethical justification for the no-screening control group, the following safeguards will be implemented: (1) Regular glaucoma-related health education and disease awareness sessions will be provided to the control group throughout the study period to help participants recognize early symptoms and understand the potential harms of glaucoma, thereby enhancing their capacity for self-monitoring and healthcare-seeking behavior. (2) A structured annual follow-up protocol will be established to collect health status data from the control arm via standardized questionnaires or digital platforms, with particular attention to monitoring symptoms such as visual acuity changes or ocular discomfort, and systematically recording any ophthalmology visits initiated by participants, including the reasons for consultation, examinations performed, and resulting diagnoses. (3) At the end of the study period, a comprehensive ophthalmic screening will be uniformly offered to all participants in the control arm to compensate for the opportunity loss resulting from the absence of regular screening during the study. (4) Periodic reports on study progress and participant health status will be submitted to the Ethics Committee to ensure ongoing adherence to ethical standards, with measures adjusted as necessary based on emerging circumstances.

To address potential parallel non-study eye care, a standardized procedure will be established to systematically collect information on all external ophthalmology encounters across all study arms at each follow-up time point. This will include optometry visits, outpatient consultations, and hospital admissions occurring outside the protocol, along with details of the healthcare facility, conducted examinations, principal findings, and clinical recommendations. These data will be incorporated as important covariates in the statistical analyses to evaluate the potential diluting or confounding effects of parallel care on the estimated effectiveness of the organized screening strategies, and sensitivity analyses will be conducted to assess the magnitude of such effects.

### Sample size estimation

2.5

The sample size calculation is based on the between-group comparison of glaucoma detection rate, which is the main endpoint of this study. Assuming that the glaucoma detection rate in the routine screening arm would approximate the reported glaucoma prevalence [approximately 3.54% (1, 19)], and that the tiered screening arm, through an optimized screening pathway, would achieve an increased detection rate of 4.54%, corresponding to a difference in detection rate (*Δp*) of 1%. Using this comparison (tiered screening versus routine screening), with a two-sided significance level of α = 0.05 and statistical power of 1 − β = 0.80, the minimum required sample size is calculated to be 6,283 participants per arm. This computation was performed using G*Power (version 3.1.9.7), employing the module for two independent proportions based on Fisher’s exact test.

The sample size is further adjusted for the cluster randomized design by applying a design effect (DEFF). Unlike chronic conditions substantially influenced by behavioral or lifestyle factors, the prevalence of glaucoma is predominantly driven by non-modifiable risk factors such as age and genetic susceptibility. Consequently, between-cluster variation in glaucoma prevalence is expected to be minimal across communities with similar demographic structures. We therefore assumed an intracluster correlation coefficient (ICC) of 0.005 (20) and an average cluster size of 40 participants, which yielded a DEFF of 1.195, approximated as 1.20, resulting in an adjusted requirement of 7,540 participants per arm. In addition, factoring in an anticipated loss-to-follow-up rate of 20%, the final required sample size increases to 9,425 participants per group (totally 28,275 participants in three groups, with *k* = 1).

### Follow-ups and outcome variables

2.6

Commencing at study initiation, participants will be prospectively followed up annually for a minimum of 6 years. Data will be collected yearly through IOP measurements, fundus photography, and follow-up questionnaires (Table 1). For patients with suspected or confirmed glaucoma, additional data will be collected including ocular optical biometry, RNFL thickness, and automated perimetry. Long-term follow-ups will track annual incidence and blindness rates of glaucoma, and quality of life among glaucoma patients.

**Table 1 tab1:** Follow-up schedule.

Groups		Visit number	0	1	2	3	4	5	6
		Visit time (year)	Baseline	1	2	3	4	5	6
No screening group		Questionnaire	×	×	×	×	×	×	×
Routine screening group		Questionnaire	×	×	×	×	×	×	×
		Intraocular pressure	×			×			×
		Fundus photography	×			×			×
Tiered screening group	High-risk population	Questionnaire	×	×	×	×	×	×	×
		Intraocular pressure	×	×	×	×	×	×	×
		Fundus photography	×	×	×	×	×	×	×
		Glaucoma specialist examination	Performed according to the screening results						
	Non-high-risk population	Questionnaire	×	×	×	×	×	×	×
		Intraocular pressure							
		Fundus photography							

All primary outcome measures will be analyzed on a per-participant (per-person) basis. The main endpoint of this study is glaucoma detection rate of the screening protocol, with sensitivity and specificity of the screening included as additional primary outcome measures. Glaucoma detection rate is defined as the proportion of participants in each arm with a final confirmed diagnosis of glaucoma in at least one eye, as determined by the reference standard examination in the screening arms or by passive case-finding through medical records in the control arm. Sensitivity is defined as the proportion of participants with confirmed glaucoma in at least one eye (as determined by the reference standard comprehensive ophthalmic examination) who are correctly identified by the screening protocol. Specificity is defined as the proportion of participants with no glaucoma in either eye who are correctly classified as negative by the screening protocol.

Secondary outcome measures include comparative analyses of the cost-effectiveness of different screening strategies and the diagnostic accuracy of physician-based versus AI-assisted image interpretation in fundus photography for screening glaucoma. The comparison of diagnostic accuracy will be evaluated at the per-participant level and will include sensitivity and specificity, as well as AUC for each interpretation method.

The cost-effectiveness analysis will be conducted from a societal perspective to comprehensively evaluate the resources consumed and health outcomes generated by different screening strategies. The primary economic outcome is the incremental cost-effectiveness ratio (ICER), expressed as the incremental cost per additional glaucoma case detected (based on observed data within the study period), and the incremental cost per quality-adjusted life year (QALY) gained (based on long-term model extrapolation). Cost components will encompass screening-related expenses, including personnel, equipment, consumables, site costs, and AI-assisted interpretation fees; diagnostic confirmation costs following referral, such as OCT and automated perimetry; subsequent treatment and follow-up costs; and direct non-medical and indirect costs, including transportation expenses and productivity losses incurred by patients and their families. Health utility values will be measured prospectively among diagnosed patients during follow-up using the EQ-5D-5L instrument and converted to utility weights using the Chinese value set. Costs and effects within the study period will be obtained through actual data collection, whereas long-term outcomes will be evaluated using a Markov state-transition model simulating the natural history of glaucoma and the long-term trajectory following screening intervention. The model will employ a cycle length of 1 year and a lifetime horizon, and future costs and health outcomes will be discounted to present value at an annual rate of 3%. Uncertainty in the incremental analysis will be assessed through one-way sensitivity analyses and probabilistic sensitivity analysis, and cost-effectiveness acceptability curves will be generated to illustrate the probability that the tiered screening strategy is cost-effective across a range of willingness-to-pay thresholds.

The questionnaire content is divided into a follow-up survey and a high-risk model assessment questionnaire. A WeChat (the most commonly used social software in China) mini-program is designed and developed to facilitate patient-completed data collection, streamlining subsequent follow-up procedures and chronic disease management. The follow-up questionnaire encompasses initial collection of patients’ demographic and clinical characteristics, along with subsequent longitudinal data acquisition, including history of glaucoma confirmed diagnosis, positive symptoms, and results of glaucoma-specific quality of life scale.

The configuration of the high-risk model questionnaire incorporates both retrospective data collection and screening for high-risk populations. Informed by currently established risk factors potentially associated with glaucoma, the questionnaire includes the following domains: age; sex; race/ethnicity; general physical constitution (degree of frailty); personal and family history of glaucoma; type and degree of refractive error; hypertension; diabetes mellitus; vasospastic disorders; migraine; anxiety; depression; Parkinson’s disease; Alzheimer’s disease; pigment dispersion syndrome; pseudoexfoliation syndrome; obstructive sleep apnea syndrome; smoking history; medication history (including steroid use, psychotropic agents, and intraocular anti-VEGF or steroid treatments) and relevant symptoms (21–26).

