This screening tool will underpin a proposed three-tiered strategy for glaucoma screening. Tier 1 Screening (Primary Screening): The pre-designed risk assessment questionnaire is administered within the community to identify high-risk individuals. Tier 2 Screening (Secondary Screening): These high-risk individuals undergo a combination of screening tests, including visual acuity, IOP measurement, fundus photography, and ocular optical biometry, which will be conducted at community healthcare or primary care centers. This stage is augmented by AI-assisted image interpretation to identify subjects suspected of having glaucoma. Tier 3 Screening (Tertiary Screening): A definitive diagnosis of glaucoma is established within the ophthalmology department of a tertiary hospital.

In the Tier 2 screening stage, fundus photographs will be interpreted using the Airdoc glaucoma-specific AI automatic screening system, which is built on a deep convolutional neural network algorithm employing an integrated multi-task learning architecture for simultaneous segmentation and classification. Standardized and traceable glaucoma grading decision rules have been established and fully integrated into the screening workflow. The system automatically performs image preprocessing, precise optic disc detection, quantitative analysis of optic disc morphology, segmentation of the optic cup and retinal nerve fiber layer defect (RNFLD) regions, and identification of glaucomatous lesions including localized RNFLD, diffuse RNFLD, optic disc hemorrhage, and optic cup notching. Moreover, it also calculates horizontal and vertical cup-to-disc ratios, ultimately generating a quantitative glaucoma risk score and a graded recommendation.

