All participants who enter the Tier 3 screening stage will undergo further examinations for definitive diagnosis, including standard automated perimetry for visual field testing, optical coherence tomography (OCT) imaging of retinal nerve fiber layer (RNFL) thickness, and gonioscopy to distinguish open-angle from angle-closure glaucoma. The final diagnosis will be made independently by two glaucoma specialists following a comprehensive review of all clinical data, with reference to internationally accepted diagnostic criteria for glaucoma, namely the presence of characteristic glaucomatous optic neuropathy with corresponding visual field defects, after excluding other ocular or neurological conditions that may cause optic neuropathy. Any diagnostic disagreement between the two specialists will be resolved by a third senior glaucoma expert who will make a final determination. To correct for verification bias, a random sample of 10% of participants who are screen-negative will also be recalled to undergo the same reference standard examination. Sensitivity and specificity of the two screening strategies will be calculated based on all screen-positive participants and the randomly selected screen-negative subset, with appropriate weighting to account for the sampling fraction.

The study is scheduled to begin patient enrollment in October 2025, with follow-up and final data collection expected to be completed in December 2032.

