### Statistical analyses

2.9

All statistical analyses will be performed using SPSS V25.0 (IBM, United States) and R software. Continuous variables will be expressed as Mean ± Standard Deviation (SD) or Median with Interquartile Ranges (IQRs), depending on the data distribution, while categorical variables will be presented as frequencies and percentages. Descriptive statistics will be used to summarize the baseline characteristics of each cohort.

Given the cluster randomized design of this study, all between-group comparisons will account for clustering effects. The comparison of the glaucoma detection rate as the primary endpoint will be analyzed using generalized estimating equations (GEE). The GEE model will employ a binomial distribution family and a logit link function, with study group as a fixed effect and community as the clustering variable, adopting an exchangeable working correlation matrix to adjust for within-community correlation. Comparisons of sensitivity and specificity will similarly be conducted using GEE to correct standard errors and confidence intervals (CIs). Cox proportional hazards regression and logistic regression analyses will incorporate cluster as a clustering variable or random intercept to identify risk factors associated with glaucoma incidence. Pearson’s χ^2^ test is utilized only for preliminary comparisons without adjustment for clustering, and final conclusions will be based on results accounting for clustering effects. A two-sided *p* < 0.05 will be considered statistically significant.

For missing data, the pattern, frequency, and possible causes of missingness will first be described. Baseline characteristics of participants with and without complete data will be compared to assess the missing data mechanism (whether missing at random). Primary outcome analyses will be performed using multiply imputed datasets, with complete-case analysis serving as a sensitivity analysis. For participants lost to follow-up after screening, sensitivity analyses using inverse probability weighting will be conducted to evaluate the potential impact of attrition on the estimation of the primary outcomes.

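### Table 1's eye-test schedule contradicts yearly collection, cannot yield annual incidence in most participants, and would bias incidence risk-factor models fitted in the tiered arm or with arms pooled

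*Protocol article*

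**What the plan says.** Section 2.6 (Follow-ups and outcome variables) states: "Data will be collected yearly through IOP measurements, fundus photography, and follow-up questionnaires". No arm is excepted. It adds: "Long-term follow-ups will track annual incidence and blindness rates of glaucoma, and quality of life among glaucoma patients".

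Table 1, which the first sentence cites, schedules the following for years 0 to 6:

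| Group | Questionnaire | Eye pressure and fundus photograph |
|---|---|---|
| No screening | every year | none |
| Routine screening | every year | years 0, 3, 6 |
| Tiered, high-risk | every year | every year |
| Tiered, non-high-risk | every year | none |

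The table matches the rest of the text. Section 2.4 says the control group "does not undergo any glaucoma screening, and the study subjects can detect and confirm glaucoma through active medical visit or opportunistic screening". Section 2.2 says of the tiered arm: "These high-risk individuals undergo a combination of screening tests, including visual acuity, IOP measurement, fundus photography, and ocular optical biometry". The flag comes from a questionnaire whose domains, listed in Section 2.6, are candidate risk factors such as age, family history, refractive error and diabetes.

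Section 2.9 then plans: "Cox proportional hazards regression and logistic regression analyses will incorporate cluster as a clustering variable or random intercept to identify risk factors". The outcome it names is incidence, and cluster is the only design feature that the sentence mentions.

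**The concern.** Three consequences follow from the schedule.

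1. Where tests are three years apart, a case found at year 3 may have begun in any of the three preceding years. Yearly incidence is not observable there.
2. Where there is no baseline eye test, a participant cannot be shown to be free of glaucoma at entry. A later diagnosis may be old disease found late.
3. In the tiered arm, the chance that a case is found depends on the covariates whose effect is to be estimated. A factor that triggers examination looks harmful even if it has no effect. This happens within communities, so a cluster term or random intercept does not remove it.

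At stake are the incidence figures and the list of risk factors the trial will report. Incidence by year and arm would partly reflect the test calendar and the baseline backlog.

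**Working it through.** **The plan's own figure.** The documents give no incidence figure. The arm size used below reproduces: the two-proportion formula with continuity correction (3.54% v 4.54%, two-sided 0.05, power 0.80) gives 6,283; 6,283 x 1.20 = 7,540; 7,540 / 0.80 = 9,425.

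**Inputs.** From the documents: 9,425 per arm, the Table 1 schedule, the 10% recall of screen-negatives (Section 2.2), and 3.54% (Section 2.5 assumes that "the glaucoma detection rate in the routine screening arm would approximate the reported glaucoma prevalence"). All other inputs are assumptions.

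**Backlog in the no-screening arm.**
- Existing cases at baseline: 9,425 x 0.0354 = 334. If 50% to 100% are undiagnosed: 167 to 334.
- New cases in 6 years at an assumed 0.1% to 0.4% a year: (9,425 - 334) x (1 - (1 - i)^6) = 54 to 216.
- Share of potentially countable cases that predate baseline: 167/(167 + 216) = 44% to 334/(334 + 54) = 86%.
- The upper end is extreme. It takes every existing case as undiagnosed, and the 3.54% is for ages 40 to 80 while enrolment starts at 18.

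**Calendar in the routine arm.** Let p be the share of cases found by self-visit in the year of onset (0 to 0.3), with constant incidence.
- Years 1 and 2: recorded rate = p, so 0% to 30% of the true rate.
- Year 3: p + 3(1 - p) = 3.0 to 2.4 times the true rate if the test finds every case. With 90% found: p + 0.9 x 3(1 - p) = 2.7 to 2.19.

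**A null risk factor.** Let d = 0.9 be the share of cases found among those examined, g the share of factor-positive people flagged, q = 0.2 to 0.4 the share of factor-negative people flagged, and p = 0.1 to 0.3 the share found by self-visit. Unflagged cases are found with probability a = 1 - (1 - p)(1 - 0.10) = 0.19 to 0.37. This credits the 10% recall and assumes it includes people negative on the questionnaire.
- Found in the tiered arm: factor-positive F = g d + (1 - g) a; factor-negative N = q d + (1 - q) a.
- Tiered ratio = F/N. Pooled ratio = (d + F + p)/(d + N + p).

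| g | q, p | F | N | Tiered | Pooled |
|---|---|---|---|---|---|
| 1.0 | 0.2, 0.1 | 0.900 | 0.332 | 2.71 | 1.900/1.332 = 1.43 |
| 1.0 | 0.4, 0.3 | 0.900 | 0.582 | 1.55 | 2.100/1.782 = 1.18 |
| 0.6 | 0.2, 0.1 | 0.616 | 0.332 | 1.86 | 1.616/1.332 = 1.21 |
| 0.6 | 0.4, 0.3 | 0.688 | 0.582 | 1.18 | 1.888/1.782 = 1.06 |

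The true ratio is 1 throughout. If the control arm's end-of-study screening also counts (replace p by 0.9 in the pooled formula), the pooled range is 2.488/2.382 = 1.04 to 2.700/2.132 = 1.27.

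**Second illustration, other assumptions.** Take true incidence of 0.2% a year in every arm, test sensitivity 0.8 and 5% a year passive diagnosis.
- Routine-arm first detections in years 1 to 6 are 0.4, 0.5, 9.7, 0.2, 0.3 and 6.2 per 1,000.
- The control arm records 11.0 per 1,000 over six years, of which 35.4 x (1 - 0.95^6) = 9.4 predate baseline.
- With 30% to 50% flagged and carrying 60% to 80% of disease, and ignoring the recall, a true high-risk v non-high-risk ratio of 3.5 to 4.0 appears as 5.6 to 6.5 (7.6 to 8.8 at sensitivity 0.6).

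**The case against.** **Different schedules are the strategies being compared.** This stands for the detection-rate endpoint, which is not affected. It does not defend incidence or risk-factor estimates.

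**The plan has safeguards.** There is a 10% recall of screen-negatives, an exit screening offered to controls, and a record of outside eye care in all arms for use as covariates (Sections 2.2 and 2.4). The recall is tied to accuracy: "Sensitivity and specificity of the two screening strategies will be calculated based on all screen-positive participants and the randomly selected screen-negative subset". Its timing is not given. Exit screening is offered as compensation. Outside-care records address parallel care, not differences that the protocol itself creates. None establishes disease-free status at entry or year of onset. The yearly questionnaire asks about confirmed glaucoma, so known cases can be removed; undiagnosed ones cannot. Section 2.4 also says baseline data are collected uniformly, but Table 1 and the description of the control arm rule out reading that as a baseline eye test for all.

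**Model details belong in an analysis plan.** This stands in part. Section 2.9 does not say that arms are pooled, list covariates or define who is at risk, so the bias is conditional on where the model is fitted. The conflict between the yearly sentence and Table 1 is not missing detail.

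**Stronger readings that a reader might infer, and that the documents do not support:**
- *That the trial would validate its own questionnaire by this route.* Section 2.2 builds the tool from literature and expert rounds and tests it on separate hospital data. The strategies are judged by weighted sensitivity and specificity. No section says the Cox or logistic models will validate or revise the tool.
- *That false-positive risk factors are the rule.* With pooled arms, 7,540 per arm, 1.5% six-year incidence, 30% factor prevalence and a design effect of 1.2, a null factor is significant 18% to 54% of the time if it always triggers flagging, but 6% to 19% at 60% flagged. No flagging rule is given.
- *That Table 1 supports no incidence analysis at all.* The routine arm can give incidence over three-year intervals.
- *That the error enters the Markov model.* Section 2.6 does not say that these rates feed it.

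**Conclusion.** The point holds in limited form. The yearly-collection sentence contradicts Table 1. Annual incidence is not observable in the routine arm, and existing disease cannot be separated from new disease in the control arm or in non-high-risk tiered participants. These conclusions follow from the schedule alone.

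The bias in the risk-factor models arises if they are fitted in the tiered arm or with arms pooled. Its direction is towards the questionnaire's own factors. Its size is not known from the documents: the pooled ratio for a null factor is about 1.06 to 1.43 on the assumptions above, and depends strongly on how often the factor triggers flagging.

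The detection-rate, sensitivity and specificity analyses, the sample size and the questionnaire's own validation are untouched. Incidence is not a listed primary or secondary outcome. The change should be made, but the trial's main conclusions do not depend on it.

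**What to change.** 1. Reword the sentence in Section 2.6 to: 'questionnaires yearly; eye tests as in Table 1'.
2. Count incidence only in participants with a glaucoma-negative baseline eye test. Report it for years 0-3 and 3-6 in the routine arm, and yearly only in tiered high-risk participants. Elsewhere call it 'rate of new diagnoses'.
3. Fit the main incidence risk-factor model in baseline-negative routine-arm participants, who are all tested whatever their risk. Use an interval-censored or discrete-time model (for example complementary log-log with two intervals) that allows for clustering. Use other arms for sensitivity analyses only. Do not add recalled tiered screen-negatives weighted by 1/0.10: non-high-risk participants have no scheduled baseline test, and one recall at an unstated time cannot show incidence.

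**Cost.** Text and analysis only; no extra visit, test or participant. The routine arm alone has fewer events. With 30% of factor-negative and all factor-positive people flagged, and 30% factor prevalence, a pooled model has 1.72 (p = 0.1) to 2.04 (p = 0.3) times as many events. Routine-only standard errors are then larger by a factor of √1.72 = 1.31 to √2.04 = 1.43, that is 31% to 43%. Onset is known only to a three-year interval. A baseline test also misses some disease: at sensitivity 0.8, 35.4 x 0.2 = 7.1 per 1,000 existing cases pass as negative, so the years 3-6 interval is cleaner than years 0-3.
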